##### 3 months

Participants in the early treatment group receive a further two sessions using the AIMhi Stay Strong app following the 3-month follow-up assessment. The two 20-min sessions occur 2–4 weeks apart and follow a similar format to the sessions received at baseline – reviewing family, strengths, worries, previous goals and sets new goals. A text message or phone call is sent 1 week following the initial treatment to remind participants of their goals and steps for making change and the time for the next session.

#### Contact control/delayed treatment- (CC/DT)

##### Baseline

Participants who are randomised to CC/DT receive 20 min of contact with the researcher using a culturally appropriate generic health App (i.e. The Hep B Story) at baseline, with a further 20-min session using the same app after 2–4 weeks. Session 1 of CC/DT goes through the structured Hep B App. Discussions specifically avoid review of family, strengths or individual goal setting. The participant interacts with the App with support from the researcher, and discussion focuses on navigation of the App and the App content. A ‘goal’ is agreed to talk to someone else in their family about the app content before the next session. A pictorial summary (utilising similar colours and images to the intervention summary) is given to the client. Session 2 reviews the information discussed in Session 1. This ensures each group receives the same contact time with researchers and interaction based on a structured App to aid participant blinding and to structure the control session. Participants receive a text message or phone call with a health tip linked with the health App in the intervening weeks.

##### 3 months

Participants in the CC/DT group then receive a 20-min MCP interview using the AIMhi Stay Strong App (on a tablet device) following their 3-month assessment, with one further 20-min session using the App within 2–4 weeks, following the format of the sessions received by the early treatment group at baseline.

#### Treatment as usual/delayed treatment (TAU/DT)

##### Baseline

Participants who are randomised to TAU/DT only receive the questionnaires and no other researcher intervention at baseline. Participants in this group receive only usual care from their renal service provider.

##### 3 months

After the 3-month assessment, participants in the TAU/DT group receive the MCP intervention, which is delivered using the same procedures as the Contact Control/DT group.

#### Fidelity of the intervention

The interventions are delivered by trained researchers who receive comprehensive training in delivery of the manualised MCP therapy and the CC activity through a two-day training workshop. The workshop is delivered by AIMhi trainers with reference to the AIMhi Stay Strong Planning Brief Treatment Manual [18], with booster sessions at 2-monthly intervals during the intervention phase. App usage data (e.g. number and type of goals and steps entered, amount of time spent on each page of the app etc) is reviewed for adherence to core MCP principles. Reviews of App data and ongoing booster sessions are used by the research team to provide regular feedback to researchers delivering treatment to redirect and adjust their mode of delivery as needed.

### Outcome measures

#### Primary outcome

##### Kessler distress scale (K-10)

K10 is a measure of psychological distress with strong links between high scores and anxiety and depression. K10 is one of the Australian Mental Health routine outcome measures and has been used in full and abbreviated forms in state and nation-wide Indigenous surveys [1, 19]. For the period July 2012–June 2013, the Australian Mental Health Outcomes and Classification Network (AMHOCN) reports mean K10 scores for ‘ambulatory’ patients with mood disorders (i.e. outpatients returning to community after being treated acutely) across Australia of 27.6 (SD = 8.5) upon return to community, 22.0 (SD = 8.5) at 91-day review, and 18.4 (7.6) upon discharge from outpatient service [20]. Considering these findings, and those of our previous study [9], a change/difference in K10 scores of 5 points is considered clinically significant. K10 is completed at baseline, 3 and 6 months follow up.

#### Secondary outcomes

##### Adapted patient health questionnaire (PHQ-9)

This tool assesses severity of depression and has shown diagnostic, criterion and construct validity [21]. It has been tested in Indigenous groups and adapted to include simplified response categories [22, 23] as well as specifically adapted for the central Australian context [24]. This culturally adapted version of the PHQ-9 is completed at baseline, 3 and 6 months follow up.

##### EuroQoL (EQ-5D) 5 level

The EQ-5D is a widely utilised multi-attribute utility instrument used for estimating utility weights for calculation of quality adjusted life years (QALYs). It is a self-report measure of quality of life in 5 domains (mobility, self-care, usual activities, pain and discomfort, anxiety and depression) and is used to calculate QALYs for the economic evaluation. Participants are supported to complete this at the time of the other assessments at baseline, 3 and 6 months follow up.

##### Healthcare resource use

The cost of delivering the intervention and total costs of health service usage (inpatient and outpatient) will be calculated. Costs will include the costs of dialysis, costs of inpatient hospitalisations and ED presentations and an estimation of outpatient health care use. Healthcare use will be based upon clinical file review.

### Sample size and power

We will recruit 156 participants over 15 months, allowing for up to 10% drop out at 6 months. With a SD of 8.5 for the baseline score and a sample of 62, 62 and 32 participants per arm, we will be able to detect a minimum difference between the group mean scores equal to 5 at 3 months with 90% power and an alpha of .05. This sample size will also give over 90% power to detect a minimum change in mean score within groups equal to 5. This calculation allows for 10% attrition. We consider a difference between the group mean scores of 5 to be clinically significant. A change of this magnitude (effect size = 0.6) suggests that the change would be positive for approximately 73% of the population.

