## Methods

### Aims

The primary aim of the study is to determine whether MCP using the AIMhi Stay Strong App reduces psychological distress for Indigenous people receiving haemodialysis, relative to delayed-treatment control groups at 3 months, and whether benefits are maintained at 6 months post-recruitment. Secondary aims test the impact of MCP using the AIMhi Stay Strong App in improving depressive symptoms, Quality of Life (QoL) and dialysis treatment adherence. We also aim to examine the cost effectiveness of this therapy.

We hypothesise that MCP therapy using the AIMhi Stay Strong App will be cost-effective and superior to both a contact control using another app (Hep B Story) [17] and usual care, in reducing psychological distress and depressive symptoms, and improving quality of life and dialysis treatment adherence at 3 months. We expect that MCP that is received in the control groups after the 3-month assessment will result in those groups showing improvements in these outcomes between 3 and 6 months.

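### The single 90% power figure does not hold for early treatment versus usual care (72–76%), and 62 per arm leaves no room for the 10% attrition said to be covered

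*Protocol article*

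**What the plan says.** Everything needed for the calculation is in the protocol article, under Sample size and power. The inputs are given as "With a SD of 8.5 for the baseline score and a sample of 62, 62 and 32 participants per arm", the difference of interest is fixed by "We consider a difference between the group mean scores of 5 to be clinically significant", and the result is "we will be able to detect a minimum difference between the group mean scores equal to 5 at 3 months with 90% power". The error rates are stated as "with 90% power and an alpha of .05", without saying one- or two-sided. The arms add up to the recruitment target (62 + 62 + 32 = 156), so they are numbers recruited, not numbers analysed.

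Attrition is mentioned twice. The section opens by allowing for up to 10% loss at 6 months, and later says "This calculation allows for 10% attrition". It also makes a claim about change from baseline: "This sample size will also give over 90% power to detect a minimum change in mean score within groups equal to 5".

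Aims sets the hypothesis for 3 months: early treatment is to be "superior to both a contact control using another app" and also superior to usual care. Randomisation gives the ratio 1:1:0.5, so usual care is about half the size of the other two arms.

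**The concern.** One power figure cannot describe both pairwise comparisons when one control arm is half the size of the other. The 90% is not limited to a particular pair, so a reader will apply it to both. In addition, 62 looks like the textbook sample size for these inputs before any inflation for dropout, which conflicts with the statement that dropout is included.

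K10 is the primary outcome, and 5 points is the trial's own threshold for clinical significance. If the comparison with usual care is null, a reader told that power was 90% would take this as good evidence against a 5-point benefit. On the stated inputs, such a benefit would be missed about one time in four.

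**Working it through.** **Inputs** (Sample size and power, unless noted): SD 8.5; difference 5; alpha .05, taken as two-sided because no side is stated; 62, 62 and 32 recruited; 10% attrition, giving 0.9 × 62 = 55.8 ≈ 56 and 0.9 × 32 = 28.8 ≈ 29; superiority required over each control (Aims).

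**Reproducing the plan's figure.** Normal formula: n per arm = 2(1.960 + 1.282)² × (8.5/5)² = 60.7, so 61. By the t-test, 61 v 61 gives 89.7% and 62 v 62 gives 90.1%, so 62 is the smallest equal arm that reaches 90%. The printed 90% is therefore reproduced by early treatment v contact control with no attrition. Adding 10% would need 61/0.9 = 67.8 to 62/0.9 = 68.9, that is 68 to 69 recruited per arm.

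**Power by comparison.** SE = 8.5 × √(1/n₁ + 1/n₂); noncentrality = 5/SE; df = n₁ + n₂ − 2; power is the probability that the noncentral t exceeds the 97.5% point of t.

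| Comparison | n | SE | Noncentrality | Power | Difference at 90% power |
|---|---|---|---|---|---|
| Early v contact control, no loss | 62 v 62 | 1.527 | 3.275 | 90.1% | 4.99 |
| Early v contact control, 10% loss | 56 v 56 | 1.606 | 3.113 | 87.0% | 5.25 |
| Early v usual care, no loss | 62 v 32 | 1.850 | 2.702 | 76.2% | 6.06 |
| Early v usual care, 10% loss | 56 v 29 | 1.945 | 2.571 | 72.0% | 6.38 |
| Early v both controls pooled, 10% loss | 56 v 85 | 1.463 | 3.418 | 92.4% | 4.78 |

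The normal approximation gives 77.1% and 73.0% for the two usual-care rows. At a 2:1 ratio, 90% power would need 93 v 47 evaluable.

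**Other readings of the inputs, for early treatment v usual care:**
- One-sided alpha .05: 85.0% (62 v 32) and 81.7% (56 v 29).
- Standardised effect rounded up to 0.6, as in the text: 77.9% and 73.6%.

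**Within-group claim.** SD of change = 8.5 × √(2(1 − ρ)), where ρ is the baseline to 3-month correlation; noncentrality = 5√n / SD of change; df = n − 1. For usual care at n = 29, power is 58% (ρ = 0), 73% (ρ = 0.3), 86% (ρ = 0.5) and 93% (ρ = 0.6). It passes 90% only when ρ exceeds about 0.51 at n = 32 or 0.56 at n = 29. In a larger arm after loss (n = 56), the same formula needs ρ of only about 0.11.

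**The case against.** Five points can be made for the plan.

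- **Pooled controls.** The primary aim refers to the delayed-treatment control groups together, and the economic evaluation compares early with delayed treatment. Early v pooled controls has 92.4% power after 10% loss. The power statement, however, gives numbers per arm, and the hypothesis asks for superiority to each control. If pooling was meant, the text does not say so.
- **A global test.** A three-group F test with means (5, 0, 0) and 62/62/32 gives 90.05%, a coherent source for one figure covering all arms. It drops below 87% at 56/56/29, and it does not test superiority to each control.
- **Timing of attrition.** The 10% is first quoted for 6 months, whereas the power claim is for 3 months. If half the loss has occurred by then (an assumption), 59 v 59 gives 88.7% and 59 v 30 gives 73.7%. This stands: the 87.0% and 72.0% are worst cases at 3 months. Even so, losing one participant per arm already takes 62 v 62 to 89.7%, and the usual-care comparison fails with no loss at all.
- **Baseline information.** The planned mixed model uses the baseline K10, which may gain precision. With variance multiplied by (1 − ρ²), 56 v 56 reaches 90% at ρ of about 0.31, so the attrition shortfall would vanish under a modest correlation. Early v usual care needs about 0.62 at 56 v 29, or 0.57 at 62 v 32. The section gives no correlation, its only SD is that of the raw baseline score, and Primary endpoint analyses controls for baseline differences only where needed.
- **The within-group claim** cannot be checked without ρ. That also stands: for usual care it is unsupported as printed, not proved false.

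**Conclusion.** The power statement is wrong as written. Two parts are firm on the stated inputs with a two-sided unadjusted comparison. First, early treatment v usual care has 76.2% power with no loss and 72.0% after 10% loss, and this comparison stays below 90% under one-sided alpha or the rounded effect size. Second, 62 per arm is the no-dropout requirement, so the attrition sentence is not supported by the numbers beside it. The resulting shortfall for early treatment v contact control is small, at most about 3 points (90.1% to 87.0%), and a modest baseline correlation would remove it. The usual-care shortfall is the serious one and would need a correlation of roughly 0.6 that the article does not state. The within-group claim is conditional: it holds for usual care only above ρ of about 0.51 to 0.56.

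**What to change.** Keep the 156 participants and rewrite the paragraph:

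1. State power separately for each comparison on evaluable numbers (56/56/29): early v contact control 87%; early v usual care 72%, with 90% power only for a difference of about 6.4 points. State that alpha is two-sided.
2. Delete the sentence saying that attrition is allowed for, or replace it with these post-attrition figures. If a smaller loss is expected at 3 months than at 6, say so and use it.
3. Limit the within-group claim to the two larger arms and state the correlation assumed.
4. If a baseline-adjusted analysis is prespecified, the adjusted figures may be quoted with their assumption. At ρ = 0.5 the SD becomes 8.5 × √(1 − 0.25) = 7.36, and power is about 94% and 83% for the two comparisons at 56/56/29.
5. If the pooled comparison is the intended primary one, Aims and the power section should both say so.

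The cost is a change of text only. Recruitment and allocation stay as they are, and the stated power becomes less favourable.

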### Statistical analyses

#### Demographic analyses

Demographic data will be tabulated and expressed as proportions and/or means of the selected characteristics by treatment group with the corresponding 95% Confidence Intervals (CI). Differences between groups will be assessed by the normal test for comparisons of means and χ^2^ tests for comparison of proportions.

#### Primary endpoint analyses

Continuous outcome measures will be compared between the three groups using a linear mixed effect model, with transformations applied to the outcome measure if not normally distributed. The mixed effect models with random effect intercept will allow for correlation between measurements of K10 scores taken at three points in time within the same subject, and will estimate the effect of the interventions at 3 and 6 months. All analyses will be conducted on an intention-to-treat basis. Preliminary analyses will check for group differences at baseline and control for them statistically if necessary.

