### Randomisation

Eligible participants are randomised following baseline assessment using a block sequential random number sequence and an envelope system of randomisation, stratified by site, level of psychological distress (high or low) and access to respite dialysis in home community. An independent statistician created the allocation schedule with a computerized random number generator and investigators are blind to this schedule. Participants are allocated to Early Treatment with MCP using the AIMhi App, Contact Control/Delayed treatment or Treatment as usual/Delayed treatment at a ratio of 1:1:0.5. Participants are assigned a Study ID following randomisation to ensure confidentiality.

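### A transformation rule triggered by the K10 distribution could move the primary analysis off the raw scale on which the 5-point criterion and the power are set

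*Protocol article*

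**What the plan says.** In the protocol article, Primary endpoint analyses, continuous outcomes are compared across the three arms with a linear mixed model, "with transformations applied to the outcome measure if not normally distributed". The section names no transformation, no test or threshold for departure from normality, and no way of bringing a transformed result back to K10 points. On the repeated measurements it says: "The mixed effect models with random effect intercept will allow for correlation" between the K10 scores at the three visits. It does not mention residual covariance, robust standard errors or degrees of freedom.

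The criterion and the sample size are in raw K10 points. Under Kessler distress scale (K-10), "a change/difference in K10 scores of 5 points is considered clinically significant". Sample size and power gives the inputs, "With a SD of 8.5 for the baseline score and a sample of 62, 62 and 32 participants per arm", and the claim drawn from them, "we will be able to detect a minimum difference between the group mean scores equal to 5 at 3 months"; the stated power is 90% at alpha .05. It then repeats the criterion: "We consider a difference between the group mean scores of 5 to be clinically significant".

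**The concern.** Two features of the transformation rule cause trouble.

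- **The trigger.** As worded, it is the distribution of the outcome. A linear mixed model assumes normal residuals and random effects; it does not require the outcome, pooled over arms and visits, to be normal. The rule can therefore call for a transformation when the untransformed model is adequate.
- **The consequence.** Once the outcome is transformed, the primary estimate is no longer a difference in mean K10. The target difference, the SD and the power were all set on the raw scale and do not carry over. Because no transformation is named, the scale of the primary test would also be chosen after outcome data are seen. That is avoidable freedom in the one analysis that should have least of it.

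At stake is whether the trial's main result can be compared with the 5-point difference it was designed to detect.

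**Working it through.** **Inputs from the protocol article.** Target difference 5 points, SD 8.5, arms of 62, 62 and 32, alpha .05, power 90% (Sample size and power). Sidedness is not stated; two-sided is assumed. K10 means (SDs) of 27.6 (8.5), 22.0 (8.5) and 18.4 (7.6) come from the external outpatient data under Kessler distress scale (K-10).

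**1. The stated power is a raw-scale figure.** For 62 v 62:

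- SE = 8.5 × √(1/62 + 1/62) = 1.527
- 5 / 1.527 = 3.275
- power = Φ(3.275 − 1.960) = Φ(1.315) = 0.906

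A three-group F test with early treatment 5 points below both controls gives 0.9005. The 90% is thus reproduced in raw K10 points with all 156 analysed. Power after dropout, or against the smaller usual-care arm, is a separate question.

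**2. The criterion has no single equivalent on a log scale.** The log is an assumption for illustration. The ratio equivalent to a 5-point fall from mean m is (m − 5)/m:

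| Mean m | Ratio for 5 points | Log difference | Points at a fixed ratio of 0.819 | Points at a ratio of 0.80 |
|---|---|---|---|---|
| 27.6 | 22.6/27.6 = 0.819 | −0.200 | 5.0 | 5.5 |
| 22.0 | 17.0/22.0 = 0.773 | −0.258 | 4.0 | 4.4 |
| 18.4 | 13.4/18.4 = 0.728 | −0.317 | 3.3 | 3.7 |

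The point columns are m × (1 − ratio). A hypothetical estimate of 0.80 would pass the 5-point criterion at a control mean of 27.6 and fail it at 22.0 or 18.4. The table is also generous: a log model estimates a ratio of geometric means, which equals the ratio of arithmetic means only under further assumptions about spread.

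**3. Moderate skewness gives little reason to transform.** A simulated K10-like distribution skewed towards its floor (mean 21.9, SD 8.4, skewness 0.67; the shape is assumed) gave a type I error of 0.050 for the untransformed t-test at 62 v 62, at 62 v 32, and at 56 v 29 (about 10% lost from 62 and 32).

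**4. The random intercept, checked separately.** With independent residuals of constant variance, a random intercept implies one common variance for every pairwise change, equal to the average of the three true change variances. The document gives no correlations between visits, so those below are assumed. For the difference between arms in change from baseline to 3 months:

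- SDs 8.5/8.5/7.6 and correlations .4 (0–3), .7 (3–6), .4 (0–6): change variances 86.7, 39.57 and 78.33, mean 68.2. SE ratio √(68.2/86.7) = 0.887, true alpha 0.082.
- Same SDs, correlations .5/.5/.25: change variances 72.25, 65.41 and 97.71, mean 78.5. SE ratio √(78.5/72.25) = 1.04, alpha 0.041.
- Equal SDs, AR(1) correlation 0.3 to 0.8: SE ratio 1.05 to 1.13 at 3 months (alpha 0.040 to 0.027), and 0.92 to 0.84 for the corresponding 6-month contrast (alpha 0.071 to 0.100).
- Equal SDs and equal correlations: ratio 1.00, no error.

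**The case against.** **On the transformation.** The clause may be shorthand for a check of model assumptions, with trigger and method left to an analysis plan that is not shown. No transformation is named, so the log figures illustrate one possible choice. Raw means can still be reported beside a transformed model, and the responder outcome in the economic evaluation is an improvement in each patient's K10, which does not depend on the mixed model's scale. Much of this stands: the defect arises only if the rule is triggered, and the 5-point criterion does not vanish from the report. But the article does not defer the choice. It states a rule, and an analysis plan that follows the rule inherits the problem. Raw means reported alongside would not be the primary estimate, and back-transforming a log effect yields a ratio.

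A reader might go further and infer that the rule will probably be triggered because randomisation is stratified by high and low distress. The document does not support that. Stratifying allocation balances the arms; it does not alter the distribution of K10 among those recruited, and no quota or enrichment is described.

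**On the covariance.** A reader might also infer that the random intercept makes the 3-month standard error wrong. That is not shown either. The article does not say that the intercept is the whole covariance structure, and residual covariance is a detail an article may leave out. The 8.5/8.5/7.6 SDs describe external outpatients at return to community, 91-day review and discharge; they are not trial visits. Nor do all arms switch treatment at 3 months: early treatment receives further sessions in a similar format, while the two delayed arms start the intervention. With assumed correlations, the error can go either way or be nil.

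**Conclusion.** The scale point holds as a conditional but real defect. The primary analysis rule lets the observed K10 distribution decide the scale, while the criterion, SD and power are fixed in raw points. If it is triggered, the primary estimate is not a difference in K10 points. Under an assumed log, the equivalent of 5 points runs from a ratio of 0.82 to 0.73 over the protocol's own quoted means. If no transformation is made, nothing is lost. How often the rule would be triggered, and how much the free choice of scale would affect type I error, cannot be judged from the document.

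The covariance supports only an optional robustness step. The size and direction of any error depend on correlations that are not given.

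**What to change.** Amend Primary endpoint analyses, and any analysis plan that repeats it, as follows:

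- State that the primary analysis is on untransformed K10 and that the primary estimate is the difference in mean K10 points at 3 months.
- Assess model fit from residuals, not from the distribution of the raw outcome.
- If residuals are clearly non-normal, report robust (sandwich) or participant-level bootstrap confidence intervals for the same difference. Given the arm of 32, use a small-sample correction with the sandwich estimator.
- Keep any transformation as a named sensitivity analysis.

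Optionally, fit an unstructured 3 × 3 covariance across the visits, or use robust standard errors, so that the result does not rely on the random intercept. An unstructured covariance has six parameters against two for a random intercept with constant residual variance, which about 140 completers (156 × 0.9) can support.

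The cost is a few lines of wording. No extra data and no change in sample size are needed. The change should be made before outcome data are examined by arm.
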